#### Phase 2: Describing the CAM Decision-Making Process Using Qualitative Methods

The second phase of the project will use qualitative research methods to achieve three goals: first, to identify characteristics of A/C received by CMP patients through A/C provider interviews; second, to explore patients' and allopathic providers' decision-making processes in choosing to use/recommend A/C; and third, to identify important outcomes and factors associated with patient and provider satisfaction. Each of these components will inform the construction of instruments for Phase 3.

### Study procedures

For this study phase, we will use qualitative methods because they can elicit the participants' perspectives in defining the range and variability of beliefs, behaviors, and experiences, all within the context of the natural language people use to discuss these issues. Qualitative methods will also allow us to discover themes not anticipated by study investigators. Standardized approaches [68-70] will guide research activities. Our data collection methods will include focus group interviews [71-74] and in-depth interviews [68,75,76], analyzed using a content analysis approach [68].

Through a descriptive case-study approach, we will investigate the full range of details of A/C use, including processes by which allopathic providers decide to make A/C referrals, how CMP patients decide to use such services, and how A/C providers decide the components of care to deliver. The primary questions that guide this case-study research are: (1) What are the barriers and facilitators to seeking/referring A/C for CMP patients? (2) What are the nature and extent of the services received from acupuncturists and chiropractors (i.e., services broader than needling for acupuncture and spinal manipulation for chiropractic care)? and (3) What are the clinical, functional, and quality-of-life outcomes patients and providers associate with receipt of A/C, and which processes or outcomes are most closely associated with patient and/or provider satisfaction?

Phase 2 qualitative data will be collected in two waves: we will use information from the first wave to refine the questions asked during the second wave interviews and focus groups and, ultimately, to collect data on potential confounders (i.e., patient factors related to decisions to use A/C services not reflected in EMR data) for use in Phase 4 analyses.

### Focus groups with patient participants

The following types of patients will be represented among those we interview: (1) patients who were clinician-referred and received A/C services; (2) patients who received A/C without a clinician referral; and (3) comparable CMP patients who have not received A/C (including those referred who did not follow through). We will use data collected through Phase 1 EMR analyses and out-of-plan surveys to identify these types of patients for sampling. We anticipate holding multiple focus groups for each category of participants. Those who received acupuncture and chiropractic care will be recruited for separate focus groups.

Focus groups are an efficient mechanism for investigating how people conceptualize, experience, and talk about issues, for examining a range or consensus of experiences, and for collecting qualitative data from many individuals in a short time. Focus groups will be audio-recorded and consist of 6-12 participants, an optimal size range for discussing behaviors and experiences [73]. Each patient focus group will address the three main topics described above. As part of that process, we will explore two additional issues related to the decision-making process as shown in the model in Figure 1: factors that prompt individuals to seek and, once initiated, continue or discontinue A/C care, and reasons for deciding to seek care with or without primary care provider concurrence. The first wave focus group results will be used to refine the draft Phase 3 questionnaires. Second wave focus groups of prior A/C users will be asked to complete the draft questionnaires prior to focus group attendance and be prepared to advise researchers on domains or questions relevant to their use of A/C services not covered in the questionnaire, as well as to comment on their understanding of the questions we designed. We will not alter questions that are part of validated instruments, but we will use the feedback to refine our overall assessment battery and to adjust items that we have created based on first-wave focus groups.

### Health care provider participants

In in-depth interviews, researchers will introduce a series of prepared, open-ended questions designed to elicit factual information on treatment (A/C providers) and referral (allopathic providers) practices, as well as providers' knowledge, beliefs, attitudes, and experiences relating to A/C for CMP conditions, including what they would perceive to be clinically meaningful improvement. An interview guide, ongoing QA meetings, and transcript reviews will assure uniformity of approach and coverage in the interviews. We will conduct in-depth interviews with acupuncturists and chiropractors who see a high volume of CMP patients from the health plan to learn about their treatment styles and decision-making processes for CMP patients as well as their experiences with KPNW members who are physician-referred or self-referred. We will also interview health plan providers, sampling from among those with high numbers of A/C referrals, those with some A/C referral history, and those who never or almost never refer CMP patients for acupuncture or chiropractic services.

### Qualitative data analysis

Audio recordings of all focus groups and interviews will be transcribed verbatim using standardized transcription protocols. Using content analysis techniques, we will analyze transcripts and field notes [68,77,78] in two stages. First, we will use topical indexing to identify text pertaining to each interview question and prompt, followed by development of a more detailed coding scheme to capture content, themes, and sentiments. Data management and reduction will be supported by use of ATLAS text analysis software (Sage-Scolari, Thousand Oaks, CA). We will compare participant responses within and across categories to identify beliefs, attitudes, behaviors, and experiences important to understanding decisions to seek and continue A/C care and outcomes associated with A/C care for CMP. We will analyze response frequency and content and the vocabulary describing concepts and experiences. This will allow identification of key issues by exploring areas of consensus and contradiction within and across focus group participants and provider respondents [68,79]. Potential bias will be minimized and data credibility enhanced through comprehensive training of interviewers and coders, and multiple members of the research team will complete each type of task. Coder reliability will be determined through check-coding of 1 out of every 6 interviews and focus groups. Because ATLAS can interface with statistical programs, participant characteristics and responses to quantitative questions (e.g., questionnaire draft) can be included in the database and will enable us to retrieve text specific to respondent subgroups.

#### Phase 3: Prospective Cohort Study to Evaluate Outcomes Associated with the Use of A/C Services

To conduct a prospective cohort study of carefully matched A/C and non-A/C patients, we will use clustering and matching methods identified in Phase 1. These matching approaches will be refined by Phase 2 qualitative findings and augmented by additional, directly assessed, patient-reported baseline data. We will follow matched patients to examine outcomes, which will include EMR (service utilization and health care costs) and patient-reported clinical, psychosocial, and QOL outcomes over a one-year prospective timeframe for each patient. We will compare outcomes from the prospective cohort to those found during Phase 1 EMR-only analyses. Specifically, we will conduct the following activities:

1. Set up a weekly surveillance tracking system to identify CMP patients referred for A/C care to allow timely recruitment of these (index) patients and two carefully matched CMP control patients.

2. Coordinate telephone or online assessments for index and comparison patients upon recruitment (baseline; prior to A/C care) and at 1-, 3-, 6-, and 12-month follow-ups.

3. Compare outcomes (clinical and psychosocial/QOL/satisfaction outcomes and health care utilization) and explore health care costs between those receiving A/C and comparison patients not receiving such services, examining relationships between patient characteristics and decisions to use A/C.

4. Conduct comparative and sensitivity analyses between results using methods that rely solely on EMR-derived data (Phase 1) with those supplemented by patient and provider data (Phase 3).

### Phase 3 participants and recruitment

***Index ***participants (i.e., those with an incident A/C referral, n = 200 acupuncture and 200 chiropractic) and matched ***comparison ***participants in this prospective portion of the study must meet the overall CMP eligibility criteria listed in Table 1 and be able to read and respond to assessment questionnaires. Both index and comparison patients must have had no A/C treatment over the previous six months to ensure that we are prospectively following a new episode of A/C care. We purposefully minimized exclusion criteria to ensure that study findings are as broadly representative of the CMP population as possible.

Health plan members will be recruited over a two-year period through a weekly EMR review to identify CMP patients referred for A/C. Those referred for A/C will be mailed an invitation to the study, including a brochure and letter describing the study, and indicating that a staff member will call soon to tell them more about the study. There will also be a study website where prospective participants can log on to learn more about the study and eligibility or opt out if they so choose. Eligible participants will be guided through the consent process and baseline assessments by an interviewer or online, according to their preferences.

### Identification of comparison participants

To recruit comparison cases for each participant in our cohort of A/C users, we will identify CMP-patient matches using the clustering/matching approach determined from Phase 1 and refined based on Phase 2 findings. As with Phase 1, participants must have a primary care visit within one month of the index patients' A/C referral so that we know that an opportunity for A/C referral existed. When an index patient enrolls online, the matching process is triggered: those matches will be located, mailed the same informational materials, and invited to enroll online. We will recruit two or more comparison participants for every index participant. A greater number of comparison participants allows a buffer of comparison participants in the event that some report A/C use during the assessment window.

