### Study Setting

This study is being conducted at Kaiser Permanente Northwest (KPNW), a large HMO in the Pacific Northwest with several features that create a uniquely favorable environment for this research. First, KPNW has an extensive history of CAM integration. Due to Washington State's 1998 law [59] mandating insurance coverage for a broad array of licensed providers (including chiropractors and acupuncturists), KPNW began to offer CAM coverage for all health plan members. Administration of this coverage is provided by a managed complementary care network that maintains electronic data from HCFA-1500 forms (including information on diagnoses, procedures, and dates of service) and these data are available to the project. Second, any health plan member can be referred by a KPNW clinician for A/C care for qualifying conditions, including acupuncture for CMP and chiropractic care for acute exacerbations of CMP conditions. Although some patients pay out-of-pocket for A/C care, our out-of-plan CAM use survey will help us discern this prevalence. Third, in 1995, KPNW implemented a comprehensive EMR system (HealthConnect) that has since captured A/C services and documented all outpatient provider encounters, diagnoses, referrals, laboratory and imaging studies, and prescriptions. The HMO provides most services in its own hospitals and clinics, yet data are compiled and available on reimbursable external services received by health plan patients. Together these provide an all-inclusive picture of members' covered health care utilization.

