### Propensity score analysis

Another method we will use to model the probability of being referred for and obtaining CAM treatment is propensity score analysis [56,59,64-66]. Propensity scoring is an increasingly accepted collection of techniques to adjust for non-random selection among groups within observational studies. This approach is designed to remove most of the imbalance associated with the *measured *characteristics of cases allowing less biased estimates of treatment effect and other quantities linked with treatment (e.g., cost, quality of life). Propensity scores are designed to extract all of the relevant information from potential confounding variables. A consequence of this method is that two people in the same propensity stratum would be equally likely to receive the (CAM) treatment, after conditioning on all their known pre-treatment characteristics, which justifies an entirely conventional analysis. We will follow the modern literature on propensity scoring to use multiple models with different forms and assumptions, as this is the only way known to probe the validity of the resulting analyses. Table 3 includes a list of EMR variables available to us for this purpose.

**Table 3 T3:** Phase 1: Variables available from EMR for Clustering/Matching Patients

Types/duration of pain condition(s)
Pain severity
Comorbid conditions (e.g., depression, obesity)
Demographics (age, gender, race, marital status, employment status)
Receipt of pain-related disability compensation
Overall healthcare service use
Prescription medications received (e.g., short and long-acting opiates, sedatives, hypnotics, and antidepressants)
Pain-related procedures received (injections, imaging, and surgeries)
Pain-related visits (primary and specialty care including physical therapy)
ER/urgent care visits
Prior use of health insurance reimbursed CAM
Characteristics of primary care provider (e.g., degree [MD, DO, NP] frequency of CAM referrals, gender)

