### Phase 3 Data Analysis

#### Patient-reported outcomes

For the patient-reported outcomes in Phase 3, we will examine differences in baseline measures between participants with and without data at the 1-, 3-, 6-, and 12-month  follow-ups. Variables related to missingness will be included in the main analyses as covariates to reduce bias in the estimates [109,110].

We will use multilevel modeling to examine differences across time in primary (pain intensity/interference/bothersomeness) and secondary patient-reported outcomes between A/C users and matched comparison participants. Two parameters (linear and quadratic slope) will characterize change across time, with linear slope capturing initial rate of change and quadratic slope reflecting the degree to which the change slowed (or increased) over time. Thus, the quadratic model for time (baseline and 1-, 3-, 6-, and 12-month follow-ups) captures nonlinear change across time. Unlike repeated measures analysis of variance, multilevel modeling does not require data at all time points from each subject, so data from all subjects will be included in analyses. Depending upon the distribution, normal, logistic, or Poisson models will be used. Importantly, these analyses can be adjusted using additional information collected from participants during the baseline assessment that we may identify in Phase 2 as influencing A/C decision-making. This will better control for factors not available during comparison patient identification when only EMR data will be available for matching/clustering.

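### Comparison patients may qualify on a primary care visit for any reason while index patients enter on a referral for pain, so regression to the mean could mimic part of an A/C benefit

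*Protocol article*

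**What the plan says.** **Index entry.** Under Phase 3 participants and recruitment, index patients are "those with an incident A/C referral, n = 200 acupuncture and 200 chiropractic". Study Setting describes the conditions for which members can be referred, "including acupuncture for CMP and chiropractic care for acute exacerbations of CMP conditions".

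**Comparison entry.** Under Identification of comparison participants, "participants must have a primary care visit within one month of the index patients' A/C referral". The stated purpose is "so that we know that an opportunity for A/C referral existed". The reason for the visit is not specified, and the sentence says the rule is shared with Phase 1. The search for matches starts only once the index patient has enrolled.

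**Common criteria.** Both groups "in this prospective portion of the study must meet the overall CMP eligibility criteria listed in Table 1" and must have had no A/C treatment for six months. Table 3 lists the record variables available for matching, among them pain severity and pain-related visits.

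**Analysis.** Phase 3 Data Analysis (Patient-reported outcomes) describes a multilevel model with linear and quadratic slopes over baseline and 1, 3, 6 and 12 months. It allows adjustment for patient-reported baseline information, to control for "factors not available during comparison patient identification when only EMR data will be available for matching/clustering". Phase 3 Sample Size says the intended analysis would adjust for baseline BPI.

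**The concern.** Time zero is defined by pain in one group and not in the other. An index patient enters because a clinician judged the pain to need a referral. A comparison patient may enter on a visit for something unrelated, during a quiet spell of the same chronic condition. Table 1 does not prevent this: its three encounters span 180 days to 18 months, so they show chronicity and not current pain. A visit for an unrelated complaint is also weak evidence of the referral opportunity that the rule is meant to establish.

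The primary outcomes are pain scores. If index patients start higher because they were caught at a bad moment, their scores fall faster whatever treatment they receive. A larger sample does not reduce this bias; it makes the bias easier to declare significant.

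**Working it through.** **Inputs from Phase 3 Sample Size.** BPI SD 2; pre-post correlation r = 0.5; effect 1 unit; two-sided alpha 0.025; 100 per group for the stated power; 200 index patients per modality with two comparisons each (200 v 400).

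**Assumed input.** Baseline gap g between index and matched comparison patients, 0.5 to 1.0 BPI point. The documents give no value.

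**The plan's own figure.** SD of change = 2 × √(2 × (1 − 0.5)) = 2.0. With 100 per group and a difference of 1, power is 90.2% (normal) or 89.8% (t), against a stated value slightly over 90%. It reproduces. At 200 v 400 it exceeds 99.9%.

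**Bias when A/C does nothing.** Follow-up scores show what remains of g. A baseline-adjusted analysis subtracts r × g from that remainder.

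- (a) The gap regresses at the correlation: r × g remains. Spurious benefit on change = g − r × g = (1 − r) × g. Adjusted: r × g − r × g = 0.
- (b) The gap is a purely transient flare: nothing remains. Spurious benefit on change = g. Adjusted: r × g.

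**Chance of a false positive, 200 v 400.** SE of the difference in change = 2.0 × √(1/200 + 1/400) = 0.173. For the adjusted analysis the residual SD is 2 × √(1 − 0.25) = 1.73, and the SE is 0.150.

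| Assumed gap | (a) change | (a) adjusted | (b) change | (b) adjusted |
|---|---|---|---|---|
| 0.5 | 0.25 (21%) | 0 (2.5%) | 0.50 (74%) | 0.25 (28%) |
| 1.0 | 0.50 (74%) | 0 (2.5%) | 1.00 (about 100%) | 0.50 (86%) |

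Entries are the spurious benefit in BPI points, with the rejection rate in brackets. Simulation (1,500 runs per setting) gave the same biases. These are simple two-group calculations on one follow-up; they do not model the matching or the multilevel structure.

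**Which columns apply.** The sample size section points to the adjusted columns. The data analysis section makes baseline one of the outcome time points, with the linear slope representing the initial rate of change. If group intercepts are free, a steeper untreated fall from baseline enters the group-by-time terms, as in the change columns. The article does not say how the two descriptions fit together.

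**The case against.** Four points on the other side have force.

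- **The visit is not the whole entry rule.** A reader might infer that any primary care attender can be a comparison patient. The documents do not support that: comparison patients must meet Table 1 and be selected by the matching method, which can use pain severity and pain-related visits. This narrows the gap. It does not close it, because nothing requires severity to be measured at the qualifying visit.
- **A pain peak is documented for one modality only.** A reader might infer that all index patients enter at a peak. Study Setting names acute exacerbations for chiropractic care and only CMP for acupuncture. Baseline is also taken after invitation and consent, when part of a flare may have passed. Comparison baselines may come later still after their visit.
- **Baseline adjustment is stated.** A reader might infer that regression to the mean will certainly appear, at a quarter to a half of the planned effect or more. In case (a) the adjustment described in the sample size section removes the bias entirely. In case (b) half survives, and the data analysis section does not clearly carry the adjustment through.
- **Matches may be refined later.** The Phase 3 overview says matching will be augmented with patient-reported baseline data, and other sections allow such data as covariates. These statements are mostly permissive, and the data analysis section says only record data are available when comparison patients are identified.

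It is also fair that a clinician may address chronic pain at a visit booked for another reason. The rule therefore weakly shows an opportunity for referral; it does not show none.

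**Conclusion.** The concern holds as a real and incompletely controlled risk, not as a demonstrated bias. The visit rule does not align pain state at entry. Any excess pain in index patients that fades without treatment would favour A/C, most plausibly in the chiropractic comparison.

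For assumed gaps of 0.5 to 1.0 point and r = 0.5, the spurious benefit runs from 0 (gap regresses at r, baseline adjusted) to 1.0 point (pure flare, unadjusted), against a planned effect of 1 point. The adjusted flare case, 0.25 to 0.50 point, cannot be removed by the analysis the plan describes. The size rests wholly on the assumed gap and on which mechanism operates; the documents settle neither.

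**What to change.** 1. Require the comparison patient's qualifying visit to carry a CMP or nonspecific chronic pain diagnosis, of the same pain type as the index patient where possible.
2. Date-match that visit to the index referral. In both groups, record the days from visit or referral to the baseline assessment and use them as a covariate.
3. Carry the baseline BPI adjustment from Phase 3 Sample Size into the model in Phase 3 Data Analysis, with baseline as a covariate and the follow-up scores as outcomes.
4. Since the article says the visit rule is shared with Phase 1, make the same change there so that the phases stay comparable.

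**Cost.** Step 1 is one more condition in the record query and must be in place before recruitment. It shrinks the matching pool. The need is 800 comparison patients over 24 months, about 33 a month (800 / 24). The 66,768 non-referred CMP members in Table 2 are an upper bound for 2010; the number who match closely and have a pain visit in the right month is not given and should be counted first. A pain code does not fully equalise position in the pain course.

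Step 3 means that participants with no follow-up score contribute nothing to that model. Adjustment is also not neutral if a gap is stable: the full g then remains at follow-up and adjustment leaves g − r × g against A/C (0.25 point for g = 0.5). This is why the entry rule should be tightened first and adjustment should not be relied on alone.

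### Comparison patients are approached only after their index patient enrolls, but their qualifying visit is tied to the index referral date, so on average their baseline falls later in the pain course

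*Protocol article*

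**What the plan says.** The protocol article fixes four points on timing.

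- **Index patients** (Phase 3 participants and recruitment). They are found by a weekly record review. "Those referred for A/C will be mailed an invitation to the study", and a staff call follows.
- **Trigger for comparison patients** (Identification of comparison participants). Nothing is done until the index patient has joined the study; at that point "the matching process is triggered: those matches will be located, mailed the same informational materials". Their own enrollment comes after that.
- **Anchor visit** (same section). Comparison "participants must have a primary care visit within one month of the index patients' A/C referral". The reason given is that a referral could then have been made. This visit is the counterpart of the referral, and so the natural time zero for a comparison patient.
- **Baseline and time axis.** Assessments start "upon recruitment (baseline; prior to A/C care") (Phase 3, activity 2). Patient-reported outcomes are modeled with "the quadratic model for time (baseline and 1-, 3-, 6-, and 12-month follow-ups") (Phase 3 Data Analysis).

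The article states no maximum interval from referral or visit to baseline. Time since the visit is not among the matching variables in Table 3 or the baseline characteristics in Table 5.

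**The concern.** The two groups share an anchor date but not a starting date. An index patient goes through one recruitment cycle between referral and baseline. A comparison patient waits for that cycle to finish and then goes through a second one, while the qualifying visit stays tied to the index referral. Months 1, 3, 6 and 12 are then counted from the later baseline.

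This matters if pain is higher when patients seek care and eases afterwards. The index baseline would catch more of the raised phase and the comparison baseline less. Index patients would then show more improvement from baseline even if A/C did nothing. Matching on characteristics up to the visit or referral does not realign the two clocks. The issue is also separate from why the visit took place, because the lag arises even when both visits are for the same complaint.

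**Working it through.** **1. The plan's own figure.** Phase 3 Sample Size gives SD 2, pre-post correlation 0.5, a 1-unit difference, 100 per group and two-sided 0.025. The SD of change is 2 × √(2 × (1 − 0.5)) = 2.0. The standard error is 2 × √(2/100) = 0.283. Power is Φ(1/0.283 − 2.241) = 0.902 by normal approximation and 0.898 by noncentral t. The stated power of slightly over 90% is reproduced and is not in question.

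**2. Lag algebra.** In days, let:
- L1 = index referral to index baseline;
- L2 = index enrollment to comparison baseline;
- V = comparison visit date minus index referral date, within one month.

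The index lag is L1 and the comparison lag is L1 + L2 − V, so the gap is L2 − V. If visits are centered on the referral, the mean gap is L2, which is positive for any recruitment delay.

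The article gives no values for L1 or L2, so I assume 7 to 42 days for each. V is taken as uniform, either over ±30 days or only up to the date of matching.
- The mean gap runs from 7 days (L2 = 7, mean V = 0) to about 54 days (L2 = 42, V uniform from −30 to 7, so 42 + 11.5).
- The share of comparison patients whose lag exceeds the index lag runs from 62% (V below 7 on a ±30 range: 37/60) to 100%.

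**3. Possible bias in points.** None of these inputs is in the article: excess pain at the anchor E = 1, 1.5 or 2 BPI points; half-life h = 4, 8 or 12 weeks; lags of 2 v 5 or 3 v 7 weeks.

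- Baseline gap: G = E × (0.5^(index lag/h) − 0.5^(comparison lag/h)).
- Gap left after m weeks: G × 0.5^(m/h).
- Bias in unadjusted change: G − G × 0.5^(m/h).
- With baseline BPI as covariate (slope 0.5 from r = 0.5 and equal SDs): 0.5 × G − G × 0.5^(m/h).

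Highest case for unadjusted change (E = 2, h = 4, 3 v 7 weeks): G = 1.189 − 0.595 = 0.59. Lowest case (E = 1, h = 12, 2 v 5 weeks): G = 0.891 − 0.749 = 0.14.

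| Follow-up | Unadjusted change | Baseline-adjusted |
|---|---|---|
| Month 1 | 0.03 to 0.31 | −0.10 to 0.02 |
| Month 12 | about 0.14 to 0.59 | 0.06 to 0.30 |

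Positive values favor A/C. Both columns are shown because the article describes a growth model with baseline as its first time point, which is closer to unadjusted change, and also says in Phase 3 Sample Size that the analysis would adjust for baseline BPI.

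**4. Effect on error rates.** The comparison is 200 v 400 at two-sided 0.025 (z = 2.241), with matching ignored.

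- Unadjusted: SE = 2 × √(1/200 + 1/400) = 0.173. Late bias of 0.2, 0.3 or 0.4 gives false-positive rates of 14%, 31% or 53%.
- Adjusted: SD = 2 × √(1 − 0.25) = 1.732, SE = 0.150, and the bias is halved to 0.10, 0.15 or 0.20. The rates are 6%, 11% or 18%, against a nominal 2.5%.

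**The case against.** The best case for the plan has five parts.

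- **The size is assumed throughout.** This stands. Delays, excess pain and half-life are all assumptions. If matches enroll within days, or pain is stable, the bias is negligible.
- **The eligibility rules select chronic pain.** Table 1 requires encounters spanning at least 180 days and counts one diagnosis per 7-day window. Study Setting mentions acute exacerbations for chiropractic only. This stands as a limit: a raised-then-settling phase is most plausible for the 200 chiropractic index patients and less supported for the 200 acupuncture patients.
- **The qualifying visit may be for any reason.** Where it was not for pain, the comparison patient has no visit-related excess to decay, and the extra delay does nothing by this route.
- **The visit may follow the referral.** The one-month window can be read both ways, so a reader who infers that every comparison baseline is a full recruitment cycle late goes too far. If visits fell two weeks after the referral, the baseline gap under the same inputs would drop to about 0.05 to 0.35.
- **Baseline data and covariates are planned.** The article adjusts for baseline BPI and allows further baseline variables for matching or adjustment. Baseline BPI adjustment about halves the late bias but does not remove it. None of the listed variables is time since the visit, so the clocks stay unaligned. The aim of timely recruitment in Phase 3, activity 1, covers both groups, but the trigger rule still delays the controls.

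**Conclusion.** The timing difference follows from rules the article states, and nothing in it realigns the groups. It holds on average, not for every pair. Where pain settles after the visit in both groups, it favors A/C, mainly at later follow-ups.

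Under the assumptions above, the late bias is 14% to 59% of the 1-unit design effect for unadjusted change and about 6% to 30% with baseline adjustment. At month 1 it is small unadjusted for most inputs, and about zero or slightly reversed when adjusted.

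A reader might infer that all three primary outcomes are biased by up to 59% of the design effect at every visit and for both modalities, or that the false-positive rate reaches 53%. The documents do not support that. Those figures are the late, unadjusted limit under assumed inputs, they rest on the BPI scale alone, and the article itself foresees baseline adjustment. What is supported is an avoidable systematic lag of unknown size that is cheap to correct before enrollment. Afterwards, baselines cannot be re-timed.

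**What to change.** Keep the enrollment trigger, but change the visit window. Choose matches whose qualifying visit precedes their own invitation by about the same number of days as the index referral preceded the index invitation. The gap then reduces to the difference in time from invitation to baseline, which should average near zero if both groups respond at similar speed.

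For every participant, record days from referral or qualifying visit to baseline, report them by group, and use them as a covariate in a sensitivity analysis. The covariate should not stand alone as the remedy, because if lag nearly coincides with group, a model cannot separate the two.

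The cost is a changed date rule in the matching program and one derived variable. There would be fewer eligible matches within each small matched group and a slightly looser calendar link to the index referral. The 66,768 members without a referral in Table 2 overstate the supply, since a match must also fall in the same group and have a visit in the window. Mailing matches together with index patients would also align the clocks, but it would recruit controls for index patients who never enroll. The sample size and outcomes do not change.
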